### Academic outcomes

Individual child-level standardized test scores will be collected from the Massachusetts DESE and used as an indicator of academic achievement. PA in children has been shown to be positively associated with scores on both Math and ELA [33, 34]. The Massachusetts Comprehensive Assessment System (MCAS) test has been used in Massachusetts annually for all students in grades 3–10. During the 2014–2015 academic year, the DESE began the process of transitioning to a different standardized test, the Partnership for Assessment of Readiness for College or Careers (PARCC). The MCAS/PARCC tests are administered annually in the spring and coincide with both mid- and post-intervention measurements. Baseline standardized test scores (year prior to enrollment) will be obtained retrospectively and for each year of participation for all participants. For both tests, raw scores are converted to scaled scores, which are linked to four levels that describe the performance levels of individual students, schools, and districts: Advanced, Proficient, Needs Improvement, and Warning. Additionally, grade-level standardized test scores will be collected across grades 3–5, and will be aggregated to analyze school-level impact of *100 Mile Club* and *Just Move*.

School attendance will be collected and examined as an exploratory outcome at the individual and school level. Attendance will be assessed as the number of days present per academic school year and converted to a percentage.

## Potential individual-level covariates

### Physical activity social support and self-efficacy

A PA social support questionnaire is administered to participants in small groups, with individuals completing their own questionnaire. The 10-item questionnaire, developed by Trost and colleagues [35], is modified from the Social Influences Scale developed and validated by Saunders et al. [36]. The modified questionnaire assesses the participant’s self-reported social support for engaging in physical activity by family, friends, classmates and teachers. Questions are answered on a three-point scale (“yes,” “no,” or “don’t know”). Example scale items include “*My mother/father/caretaker thinks I should be physically active*,” “*The students in my class think I should be physically active*,” and “*My teacher has encouraged me to be physically active in the last two weeks.*”

Participants also complete the “What Kind of Kid Are You?” 18-item questionnaire which is designed to assess how children evaluate themselves in various domains including athletic competence, behavioral conduct, and global self-worth. Questions are taken from the Harter Self-Perception Profile for Children [37]. Participants are asked which of two opposing statements best describes them and then whether it is “sort of true” or “really true” for them. This structured alternative format is designed to minimize socially desirable responses and ensure internal consistency and reliability [38].

### Dietary intake

Dietary patterns are collected by child self-report using two instruments, both administered in small groups. One questionnaire focuses specifically on weekday breakfast consumption, and the other is a 7-day recall focused on diet quality. The 6-item breakfast questionnaire developed for this study asks about typical weekday breakfast consumption, including whether or not the participant usually eats breakfast on school days, source of breakfast (school, home, restaurant), and foods and beverages typically consumed for breakfast. The same questions are asked about “today” (the day of data collection). Breakfast consumption has been linked with stronger cognitive functioning in children [39] and data on breakfast consumption will be explored as a potential covariate or moderator of intervention effects on cognition.

Diet quality is assessed through a 39-question 7-day recall. Research assistants explain to participants how to complete the questionnaire. The FLEX Dietary Questionnaire is adapted from several published, validated instruments [40–42]. The recall is divided into 5 categories: beverages, fruits, vegetables, salty snacks, and sweet snacks. The structure is similar to the Block Food Frequency Questionnaire for Ages 8–17 [43] in which respondents indicate how many days in the last week they consumed an item (none, 1 day, 2 days, 3–4 days, 5–6 days, or everyday) and how much they had in one day (a little, some, or a lot). The Block Food Frequency Questionnaire for Ages 8–17 was used during Wave 1, but field administration showed the foods included to be less relevant to the consumption patterns of the study participants and the format (scantron form) to be challenging for the 8–10 year old participants to complete. Foods and beverages included in the FLEX Dietary Questionnaire, administered in Wave 2, reflect the foods and beverages frequently consumed by children in this age group as well as foods and beverages to limit (sugar-sweetened beverages, salty snacks, desserts) and those to promote (fruits, vegetables, water) [44]. The portion size for each item is matched to a standard serving size to represent “a little” (1/2 standard serving), “some” (1 standard serving) and “a lot” (1.5 times standard serving). A final question asks how many days the respondent has eaten out (including restaurants, fast-food, or take-out) in the last 7 days. Each questionnaire receives an overall score for diet quality and will be used as a covariate in analyses.

### Fitness assessment

Cardiorespiratory fitness (CRF) is measured as a covariate using the FITNESSGRAM^®^’s Progressive Aerobic Cardiorespiratory Endurance Run (PACER) test, which is a 20-meter maximal-effort shuttle-run. The 20-meter shuttle-run has been validated with young populations [45] and shown to be highly correlated with VO_2_max in children [45, 46]. The test is administered once per school year (for 2 school/study years) in the study schools by trained research staff who follow a standard protocol based on the Cooper Institute’s published guidelines [47]. Aerobic capacity as measured by the PACER will be analyzed using standards described by FITNESSGRAM [47].

## School level data

The study champion/liaison at each school (ex. principal or other administrator, PE teacher, health coordinator) is asked to complete a short, 14-item online survey, which assesses the PA environment (PAE, including practices and policies). Questions from the PAE were adapted from the School Physical Activity Policy Assessment (S-PAPA) [16, 48]. The survey is divided into sections to assess PA-supporting policies and practices in four areas relevant to the school environment: PE, recess, classroom-based PA, and before- and after-school PA opportunities. Scores on the PAE scan will be tabulated based on policies and practices identified as being related to children’s MVPA during school [16, 49]. Total point scores will also be either median-split into high- and low-PAE or stratified by percentile (low = 10th percentile, medium = 50th percentile, high = 90th percentile) for analysis.

The champion/liaison at each school is also asked complete an online, 14-question survey about the school food environment, policies, and practices. Questions are divided into categories including breakfast, snacks, competitive foods, and other nutrition or healthy eating programming that the school is participating in and were drawn from categories included in school wellness assessment tools [50]. Both the school PAE scan and the school food environment survey are completed once per school year.

Other school-level data collected will include PE schedules and lunch and recess times. These data will be linked to individual participants and potentially included in analyses to explore impact on cognitive outcomes (i.e. whether timing of lunch/recess/PE relative to participants’ completion of cognitive tests relates to performance).

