## Interventions

The *100 Mile Club* is a school-based program that encourages children to walk, run, or wheel 100 miles over the course of the school year (approximately 3 miles per week). The program can be implemented before, during, and/or after school depending on the school schedule and is led by one or two champions (e.g., PE teachers), identified by school administration, who log student miles. Champions are encouraged to tally participants’ miles each week and display participant and school progress in a prominent location. The goal is to encourage participants and provide positive feedback and reinforcement. Champions are trained by study staff and are provided materials, resources, and ongoing support for implementation throughout the duration of the intervention.

*Just Move* is a program of structured classroom-based, PA breaks that integrates both high- and low-intensity movements (ex. jumping jacks, squats, stretches, yoga) with academic material to provide children with opportunities for engaging in PA while learning. Breaks are designed to be short (5–15 min), and teachers are encouraged to incorporate at least one break per day. *Just Move* activities are presented on cards with a picture of the movement and suggestions for connecting the moves with academic subjects like math, language arts, and science. Study staff train teachers to implement the activity breaks and provide a set of cards along with strategies and ideas for making the breaks fun and engaging for their students and low-burden for the teachers themselves. Study staff provide ongoing support to classroom teachers throughout the intervention to help ensure that teachers continue to implement *Just Move* breaks in their classrooms.

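### Grouping the school PA-environment score on 24 schools wastes information, and a score taken after programme start can be affected by arm

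*Protocol article*

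**What the plan says.** The School level data section describes an online survey of the school's PA environment. On the respondent: "The study champion/liaison at each school (ex. principal or other administrator, PE teacher, health coordinator) is asked to complete a short, 14-item online survey". The survey has sections on "PE, recess, classroom-based PA, and before- and after-school PA opportunities". On scoring: "Scores on the PAE scan will be tabulated based on policies and practices identified as being related to children’s MVPA during school". On grouping: "Total point scores will also be either median-split into high- and low-PAE or stratified by percentile", with the percentile option defined as "low = 10th percentile, medium = 50th percentile, high = 90th percentile) for analysis".

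On timing: "Both the school PAE scan and the school food environment survey are completed once per school year". Table 1 agrees. The PA environment scan is ticked only in the yearly column and has no baseline tick, whereas the champion/teacher questionnaire has one.

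The Interventions section says that Just Move "is a program of structured classroom-based, PA breaks", and of 100 Mile Club: "The program can be implemented before, during, and/or after school depending on the school schedule".

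**The concern.** There are two separate issues.

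The first is the grouping. A graded score on 24 units is to be reduced to two or three classes, and the choice between two rules is left open. Any result by PAE level would be less precise than the data allow and could depend on the rule chosen. The percentile option is also unclear. It names three points rather than bands, so a school at, say, the 30th percentile has no defined class.

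The second is timing and content. Classroom activity and before- or after-school activity are among the scored areas, and the programmes work in those areas. The year-2 survey falls during the intervention. Arm assignment was released to recruiting staff once a school had agreed to take part, so the year-1 survey may follow assignment too. If such a score defined strata or entered a model for the programme effect, arms would be compared within groups that the programmes had partly shaped.

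**Working it through.** The article gives no figure for any PAE analysis, so there is none to reproduce.

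**Inputs.** 24 schools (Setting & participants). Three arms, with schools randomised in blocks of three (School recruitment & randomization). Equal arms of 24 / 3 = 8 are an assumption, because arm counts are not given in the text. The normal score, the linear relation and the size of any programme effect on the score are also assumptions.

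**1. Median split.** For a standard normal score X split at its median, the correlation between X and the ±1 indicator is E|X| = √(2/π). The share of information on a linear slope that is kept is its square:

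2/π = 0.637, a loss of about 36 %.

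Simulating 24 normal scores gave 0.638. As an illustration, take a school-level test of the PAE slope with 80 % power on the continuous score (two-sided 5 %):

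- expected z = 1.960 + 0.842 = 2.802
- after the split: 2.802 × √0.637 = 2.236
- power = Φ(2.236 − 1.960) = Φ(0.276) ≈ 61 %

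**2. Percentile strata, if 10th and 90th are cut-points.** 0.10 × 24 = 2.4 schools per outer group, or 2.4 / 3 = 0.8 per arm. Whole-number splits are 2/20/2 or 3/18/3. The simulated share of score variance lying between groups was 54 % and 66 % respectively, a loss of 46 % or 34 %.

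**3. Percentile values, if 10th, 50th and 90th are only points at which a continuous fit is read off.** Nothing is lost.

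**4. Dependence on arm.** Simulation of 16 programme and 8 control schools, with the programme raising the score by an assumed number of SDs, and a median split over all 24:

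| Assumed shift (SD) | Control schools classed high | Programme schools classed high |
|---|---|---|
| 0 | 50 % | 50 % |
| 0.5 | 37 % | 57 % |
| 1.0 | 25 % | 63 % |
| 1.5 | 15 % | 68 % |

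At a 1 SD shift about 2 of 8 control schools are high, and in 34 % of simulated trials at most one is. This shows how far the classes could come to stand in for arm. It does not estimate bias in a programme effect, and the article gives no basis for choosing a shift.

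**The case against.** Five points can be made for the plan.

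- The grouping sentence says that totals will *also* be grouped, after saying that scores will be tabulated. The ungrouped score is therefore apparently kept. This stands, and it limits the information loss to analyses that use the grouped version.
- The 10th, 50th and 90th percentiles are points and may be evaluation values of a continuous fit. This is possible. The verb used is *stratified*, which favours classes, but the text does not settle it. The figures for outer groups hold only on the cut-point reading.
- No model that conditions on PAE is stated. The examples of covariates in the analysis section are sex, race/ethnicity and weight status. This stands, so the dependence on arm matters only if a post-start score is used in that way.
- The 14 items are not shown. A reader might infer that later surveys will class programme schools as high because of their arm. The documents show overlapping subject areas, not that the items count the study programmes, so only *can* is supported.
- Details of PAE modelling may sit in a fuller plan that is not shown. That covers the choice of rule and survey year. It does not cover the commitment to group the score for analysis, which the article makes itself.

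**Conclusion.** The point holds as a minor one about secondary analyses. Grouping by the median discards about a third of the information on the PAE relation, given a roughly normal score and linearity. With 10/90 cut-points the loss is 34 to 46 %, and the outer groups are too small to be represented in every arm on average. The continuous score avoids both problems.

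The dependence on arm is conditional. It needs a score taken after programme start, items that register the programmes, and use of that score as stratum, moderator or covariate. If all three hold, the comparison could be distorted, in a direction that cannot be stated from the documents.

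A reader might also take the 64 % to mean that the trial works as if it had about 15 schools (0.637 × 24 = 15.3). That is not supported. The figure concerns the PAE slope only, and the unadjusted comparisons of each programme with control do not use the score.

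**What to change.** Replace the grouping sentence with a statement that the PAE score is analysed as continuous, with an arm × score term if moderation is examined. State that the 10th, 50th and 90th percentiles are only values at which the fitted effect is displayed.

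In any effect or moderation model, use the year-1 score only where it describes the school before the programme began. Otherwise use a score that omits items counting the study programmes. Do not use the year-2 survey in these models.

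No new data are needed, but there are costs. Linearity has to be assumed and is hard to check with about 8 schools per arm. A pre-start survey may not exist for every school, and a score with items removed measures a narrower environment than the full one.

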## Process evaluation

To better understand implementation of the intervention programs (*100 Mile Club* and *Just Move*), several process measures are being collected in the intervention schools. Children are asked to complete a short questionnaire at both midpoint and post-intervention to assess program participation, acceptance, and sustainability.

School champions, in both *100 Mile Club* and *Just Move* schools, and classroom teachers implementing the *Just Move* program, are asked to complete brief surveys at baseline, midpoint, and post-intervention. Questions are designed to gather information on frequency and dose of the programming. In addition, questions assess factors related to implementation including facilities and resources used; leadership and modeling of PA behaviors; strategies for engagement; and perceptions of the program by school administration, other staff, parents, and children.

Direct observations of the programming are conducted in each of the intervention schools, once per school year. Using a standard rubric for the observation, study staff will document numbers of children participating, engagement of participants, and resources being used. Communication with champions and classroom teachers about program implementation will be documented systematically.

## Sample size calculation and data analyses

A priori sample size calculations for the FLEX study were based on several recent school-based physical activity interventions. Power calculations for our analysis with respect to school-time MVPA were based on the findings of Verstraete et al. [51]. In this study, the intervention group showed a greater percentage of recess time spent in MVPA, compared to controls (mean ± SD: 53.4 ± 25.6 vs. 43.5 ± 27.6). While we expect a larger difference from our more intensive intervention, we used this conservative estimate to calculate our sample size, resulting in an estimated sample size of 115 participants per arm (total *n* = 345) with power of 80 %. For total daily MVPA, we referred to the findings from a RCT to increase PA through curriculum modification by Donnelly et. al [52]. In this study, the intervention group received 90-min/week of physically active classroom lessons (≈10 min/lesson) which resulted in an increase of 26 min of weekly MVPA in the intervention group compared to controls (within group SDs = 40). We estimated that a sample size of 39 per arm (117 total) is needed to detect differences of this magnitude. Thus, the sample size of 345 will be sufficient. Because the number of clusters is fixed at 21 schools, 7 per arm, we used a protocol suggested by Hemming et al. [53] to adjust for the clustering. Assuming an ICC of 0.03 and attrition rate of 25 % per year, we arrived at a final sample size of 903 students, 43 per school.

During the 2014–2015 study roll out, Boston experienced a severe snow season which impacted the school recruitment process. After consulting with the funding agency we subsequently extended school recruitment and intervention implementation into the next year, creating the two-wave structure described previously.

For statistical analyses, descriptive statistics for variables of interest will be compiled and tabulated. To test the effect of school-based PA programs on minutes spent in MVPA, we will compare *100 Mile Club* vs. control and *Just Move* vs. control as separate tests using mixed effects models. Outcomes of interest are changes in minutes of MVPA between midpoint vs. baseline and post-intervention vs. baseline. The key regression coefficient of interest is the intervention by time interaction term, which will indicate if the intervention is associated with a significant higher/lower change in MVPA across time compared to the control. The unique school identification number will be modeled as random intercepts to adjust for clustering. We will examine both unadjusted and adjusted (including covariates such as sex, race/ethnicity, weight status) regression coefficients of the respective program and conclude if the difference in MVPA minutes is statistically significant. A similar approach will be used to examine the impact of PA programming on academic/cognitive outcomes. All analyses will be performed using SAS 9.3 (Cary, NC, USA) and results with p-values less than 0.05 will be considered statistically significant.

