## Methods/Design

### Aims

The primary aim of the FLEX Study is to evaluate the impact of two school-based PA programs, *100 Mile Club®* and *Just Move™*, on children’s school-time MVPA and total daily MVPA, compared to a control group. In addition, the RCT will evaluate the effects of these innovative, school-based PA programs on children’s cognitive performance and academic achievement. The study will also evaluate the reach of the programs by examining factors that influence participation among different demographic, weight status, and fitness groups.

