## Primary outcomes

### Physical activity

Waist-worn tri-axial accelerometers are used to objectively measure participants’ physical activity (Actigraph accelerometers, models GT3X+ and wGT3X-BT, ActiGraph, LLC, Pensacola, FL) and have been validated and calibrated for use among children [26]. Study staff instruct each participant how to wear the accelerometer. Participants are asked to wear accelerometers during all waking hours, except when bathing or swimming, for 7 consecutive days. Accelerometers are initialized to store activity counts beginning at 00:00:01 on the first day the child will wear the device; data will be processed using a 15-s epoch. To support wear-time compliance, participants are also given a paper calendar-style tracking log on which they are instructed to write down the time they put the accelerometer on each morning and the time they remove it before bed each night. The log also asks participants to self-report any days they were ill during the wear week, as well as any sports or physical activities they played during the wear week and their favorite sports/physical activities. In addition, weather data are collected from the National Oceanic and Atmospheric Administration (NOAA) [27], and the high temperature (continuous) and precipitation (binary: yes/no) are recorded for each day accelerometers are worn. Data are collected from the weather station nearest to the participating school.

Accelerometer data will be categorized into minutes of sedentary, light, moderate and vigorous activity using thresholds developed specifically for children [28]. In-school and out-of-school time MVPA will be extracted. In-school hours will be calculated for each participant based on specific start and end times of the school day for each day the accelerometer was worn. Weekday out-of-school time will be calculated as the sum of before school time and after school time, accounting for school hours and average awake time.

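### The 80 % power stated for school-time MVPA is calculated from percentage of recess time, while the trial analyses change in minutes over the whole school day, and no conversion is given

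*Protocol article*

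**What the plan says.** The Aims section sets two primary comparisons: "school-time MVPA and total daily MVPA, compared to a control group". Under Primary outcomes, Physical activity, the in-school window is the full school day: "In-school hours will be calculated for each participant based on specific start and end times of the school day". The analysis paragraph of Sample size calculation and data analyses fixes the quantity tested: "Outcomes of interest are changes in minutes of MVPA between midpoint vs. baseline and post-intervention vs. baseline".

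The sample size paragraph of the same section makes two calculations.

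- **School-time MVPA.** The source is a school trial in which "the intervention group showed a greater percentage of recess time spent in MVPA, compared to controls", with means ± SD of 53.4 ± 25.6 and 43.5 ± 27.6. The article expects a larger difference in FLEX and says "we used this conservative estimate to calculate our sample size". The result is 115 per arm, 345 in total, at 80 % power.
- **Total daily MVPA.** The source is a trial of active classroom lessons, "which resulted in an increase of 26 min of weekly MVPA in the intervention group compared to controls (within group SDs = 40"). The result is 39 per arm, 117 in total, followed by "Thus, the sample size of 345 will be sufficient".

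The figure is then adjusted for 21 schools (7 per arm), an ICC of 0.03 and 25 % attrition per year, giving 43 per school and 903 children.

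**The concern.** The first calculation is labelled as power for school-time MVPA, but it describes another quantity (a percentage), in another window (recess), with an SD that belongs to that percentage. This is more than a change of unit. Recess is one part of the school day, and the spread between children in school-day minutes also reflects PE, lunch, classroom time and movement between them. A standardised effect of 0.37 within recess equals 0.37 over the school day only if the ratio of effect to SD happens to be the same.

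The interventions do not supply the link. According to the Interventions section, *Just Move* is classroom breaks, and *100 Mile Club* may run before, during or after school. Activity before or after school falls outside the in-school window.

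What is at stake is how a result will be read. A null finding on school-time MVPA would be set against a stated 80 % power that was worked out for something else. Because 115 is the larger of the two requirements, it also fixes 345 and 903, so the whole sample size rests on the recess input.

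**Working it through.** **1. Reproduce the plan's figures** (two-sided 5 %, 80 % power; sidedness is not stated, but one-sided versions give 90 and 30 and do not match).

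School-time calculation:
- Difference = 53.4 − 43.5 = 9.9 points
- Pooled SD = √((25.6² + 27.6²)/2) = 26.62
- d = 9.9/26.62 = 0.372
- n per arm = 2(1.960 + 0.842)²/d² gives 114. The t-test version gives 114.5, so **115**, as stated. Power at 115 is 0.805.

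Total daily calculation:
- d = 26/40 = 0.65. The normal formula gives 38 and the t-test version 38.1, so **39**, as stated.

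Cluster step for a fixed number of clusters:
- m = n(1 − ICC)/(k − n·ICC) = 115 × 0.97/(7 − 3.45) = 31.4, so 32
- 32/0.75 = 42.7, so 43 per school; 43 × 21 = **903**

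The arithmetic is sound, and 903 follows from the recess-based 115.

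**2. What carrying 0.372 to school-day minutes requires.** If recess lasts R minutes and the effect is confined to it, the effect is 0.099R minutes. The standardised effect stays at 0.372 only if the school-day SD equals 0.266R. The article gives neither R nor the SD. A sensitivity range at 115 effective per arm, with **both R and the SD assumed**:

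| Recess (assumed) | Effect, min | SD 6 min | SD 8 min | SD 10 min |
|---|---|---|---|---|
| 20 min | 1.98 | 0.706 | 0.467 | 0.323 |
| 30 min | 2.97 | 0.964 | 0.804 | 0.615 |

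Power falls on either side of 80 % depending on inputs that the article does not supply. The range also says nothing about effects outside recess, which is where both programmes may act.

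**3. Total daily MVPA.** If 40 is a weekly SD, effect and SD divide by the same constant and d stays at 0.65:
- over 7 days: 26/7 = 3.7 min/day, SD 40/7 = 5.7 min/day
- over 5 days: 26/5 = 5.2 min/day, SD 40/5 = 8.0 min/day

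The 39 per arm stands on either basis. The implied daily SD is not stated, so a reader cannot compare it with the data.

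**4. The trial as enrolled.** Study design gives 24 schools, and Data collection methods gives 174 + 1,008 = 1,182 children. Assuming 8 schools per arm of equal size and ICC 0.03, there are 1,182/24 = 49.25 per school.
- After one 25 % loss: m = 36.9; effective n = 8 × 36.9/(1 + 35.9 × 0.03) ≈ 142 per arm; detectable difference 2.802 × √(2/142) ≈ 0.33 SD
- After two 25 % losses: m = 27.7; effective n ≈ 123 per arm; detectable difference ≈ 0.36 SD

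These are in SD units. Turning them into minutes needs the SD that the article does not give.

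**The case against.** The strongest reply is that nothing is miscalculated. The article names its source trials and its recess metric openly, and borrowing a standardised effect from the nearest comparable trial is common planning practice. It expects a larger effect than the one borrowed, neither programme is confined to recess, and enrolment passed the target. All of that stands, and it limits the finding to an unsupported basis. It does not close the gap. The article never says that it is carrying over a standardised effect, and *conservative* compares effect sizes without addressing the SD of school-day minutes.

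Two stronger readings are tempting.

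- **The trial is underpowered.** The documents do not show this. Every low value in the sensitivity range comes from an assumed SD and recess length, at 115 effective per arm, although enrolment may give about 123 to 142.
- **The total daily MVPA calculation mixes weekly and daily units, so calling 345 sufficient fails unless the daily SD is at most 10 min.** The SD of 40 is attached to the weekly figure and most naturally reads as weekly, in which case d and 39 per arm are unchanged. The 10-minute limit depends on dividing 26 by 7. Dividing by 5 school days, which is as defensible for a classroom intervention, puts the limit at about 14 min (5.2 divided by 2.802 × √(2/115) = 0.369). No fixed threshold follows from the article.

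**Conclusion.** The point holds for school-time MVPA. The stated 80 % power, and the 115, 345 and 903 derived from it, belong to percentage of recess time. The analysed outcome is change in school-day minutes, for which the article gives no effect, no SD and no conversion. Describing the estimate as conservative is likewise unsupported for that outcome.

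The size of the discrepancy in power cannot be fixed from the documents, and its direction is unknown. The figures that rest on the documents alone are d = 0.372 and the chain 115, 345, 903. The effective sample sizes of 123 to 142 rest on equal allocation, equal school sizes, ICC 0.03 and one or two 25 % losses.

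For total daily MVPA, the calculation is consistent on the weekly reading of the SD. What remains is a point of reporting: the unit of the SD and the implied daily values should be given.

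The choice of estimand, test and model is untouched. This is a stated figure worth correcting, and it does not threaten the trial's validity.

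**What to change.** Keep enrolment unchanged and make these edits to Sample size calculation and data analyses.

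1. Restate power, or the minimum detectable difference, in minutes of change in school-time MVPA and in total daily MVPA, for the 24 schools and 1,182 children enrolled. Take the SD and ICC from FLEX baseline accelerometry. Because the outcome is a change, state the assumed baseline-to-follow-up correlation ρ; with equal variances, SD of change = baseline SD × √(2(1 − ρ)). Alternatively, say plainly that d = 0.37 is carried over as a standardised effect from recess to the school day, and justify it.
2. Remove the word *conservative* unless that recalculation supports it.
3. For total daily MVPA, state the unit of the SD of 40 and the implied daily effect and SD (3.7 and 5.7 min over 7 days, or 5.2 and 8.0 min over 5 days), and set them beside the baseline values.
4. Present any table of power against SD as a sensitivity range on assumed values, with no fixed cut-off for keeping or deleting the statement that 345 is sufficient.

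The cost is a short recalculation from data already collected. The stated power may become less favourable.
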